### Statistical Analyses

All primary analyses will be conducted on an intent-to-treat basis. Secondary analyses will explore dose-response effects among those with variable levels of adherence to the intervention. All analyses will be two-sided, and the alpha error will be set at .05. We will begin our analysis by examining univariate statistics (means, medians, SDs, and 95% CIs) and distributions. We will examine the balance of participant characteristics by study groups and account for any imbalances in our multivariable analysis. As appropriate, differences in measured characteristics (ie, demographics and prebaseline smoking behaviors) by group will be tested using Chi-square tests of independence (categorical variables), analysis of variance (continuous variables), or the equivalent nonparametric tests, depending on the distribution of the variables. Differences in baseline characteristics of the intervention and comparison groups will be assessed.

To test Hypothesis 1, we will categorize the smokers as either African Americans or not, and then use the chi-square statistic to test for differences between the peer recruitment and standard groups. We will also compare mean recruitment time between the two types of recruitment method using a *t* test. We will explore possible factors that may not be balanced between the smokers recruited from the two methods. If we find any significant differences, we will develop a linear regression model to further adjust for the influence of the confounders on the time to recruitment outcome. Within the peer recruitment groups, we will conduct a secondary analysis examining differences in demographic characteristic between peer recruited and directly recruited smokers. Using data provided by search engine advertisement managers, we will evaluate the performance of our online advertisements (number of users registered on Decide2Quit following an advertisement on the search engine).

To test Hypothesis 2, we will use a generalized linear model, which includes indicators of peer recruitment and recommender CTHC and the interaction between the two indicators as independent variables.

To test Hypothesis 3 (effectiveness), we will compare participants randomized to enhanced CTHC and those randomized to standard CTHC. We will use the 7-day point prevalence cessation of the 6-month follow-up as the dependent variable in generalized linear models. Using mediation analysis, we will examine the potential mechanisms through which we anticipate the intervention to produce a beneficial effect. We will categorize the NicAlert test into smokers and nonsmokers’ categories and use the Chi-square statistic to test for differences. If risk reduction (decreased number of cigarettes smoked) is normally distributed, we will use the identity link function in the generalized linear model. We will also model risk reduction using count regression with a Poisson or negative binomial regression modeling if the variance of the distribution of risk reduction is over dispersed. For Hypotheses 2 and 3, we will compare African American smokers across the groups, and African American and white smokers for heterogeneity.

To assess the difference in smokers comparing the peer recruitment and standard recruitment, we will use a three-step strategy. First, we will collect data on covariates (minority status, education, readiness to quit, and income) that have been shown to differ between the peer recruitment and standard recruitment [26]. We will use these variables to adjust our overall models with the outcome of smoking cessation, comparing participants from peer recruitment and those from standard recruitment. Second, peer recruitment is, in many ways, analogous to clustering. Each person who is recruited by another individual is clustered in the group of the initial peer recruiter. Thus, some component of the difference is within the relationship between recruiter and recruitee. To address this issue, we included a marker for each “recruiter” as a fixed effect in the model. Third, we will use an advanced approach, termed complier-averaged causal effect analysis (CACE), to compare those who complied (peer recruited or not) in the intervention group with those who would have complied in the comparison group if they had been exposed to the intervention (peer recruitment). Thus, after adjustment using the first and second approach, we will conduct additional models using CACE.

For the budget impact analysis, we will compare the costs of the four intervention arms from the perspective of an implementing organization. The research team will track staff time associated with each intervention arm, including time for training, recruiting, and administering the different aspects of the intervention such as incentives for recruitment. In addition, we will work with the research team to estimate development costs of each intervention component (eg, the adaptive component of the CTHC) and any equipment or supply costs. We will compare the costs of the different intervention arms in multiple scenarios in which we examine how costs change based on changes in the components of the intervention and the types and amount of staffing provided for implementation. The economic analyses for will primarily consist of descriptive statistics. Using the estimates of costs of supplies, equipment, and staff time and the potential savings that result from decreased health care costs related to smoking cessation, we will calculate the budget impact of implementing a particular treatment strategy from the perspective of an implementing or disseminating organization. We will follow the guidelines outlined for best practices in budget impact analysis [43]. We will create tables to describe the assumptions of our inputs and outputs of our budget impact analysis and perform sensitivity analyses to examine how changing the assumptions of the model impact the potential costs for an organization implementing the intervention.

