## Methods

### Study Overview

The goal of this study (ClinicalTrials.gov: NCT03224520) is to recruit 1200 smokers to test our effectiveness and dissemination hypotheses. To participate in the study, all smokers will register online for the Decide2Quit DISC. Randomization will occur after registration using a multilevel approach, as detailed below. We will follow smokers for 6 months from their registration date. Following a description of the intervention and comparison, our protocol is described in detail below. The protocol of our study was approved by the Institutional Review Board at the University of Massachusetts Medical School.

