### Study Design

As noted in Figure 1, all participants registering online on the Decide2Quit DISC will first undergo an effectiveness randomization and then a peer recruitment allocation. The effectiveness randomization will randomly assign participants to either receive access to the recommender system CTHC or the standard CTHC. The peer recruitment allocation will depend on the recruitment source. As noted in the section below, we will either directly recruit participants to the study (via search engine advertisements and research match) or they will be recruited by their peers (peer recruited). Directly recruited peers will be randomized to either receive the peer recruitment toolset or not receive the toolset. All peer recruited participants will receive access to the peer recruitment toolset. We are using this approach for the peer recruited smokers to enhance blinding. This decision was made because these recruited smokers may communicate with their peers about the intervention.

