#### Website Engagement and Feedback: Implicit and Explicit

We will use repeated use over other use measures (number of logins) to measure website engagement, as this has demonstrated an association with smoking cessation [39]. This is an ordinal scale of the number of Decide2Quit functions used after the first DISC visit (0: no functions used; 1: use of 1-2 functions, 2: >2 functions used). We will also continuously assess explicit (influence survey) and implicit (days to click on website) feedback after each email sent. When a smoker is sent an email, we will include a link to rate the message on the influence scale.

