### Sample Size

#### Hypothesis 1: Dissemination

Our previous work [26,27] showed that having access to peer recruitment increased the proportion of African Americans to 23%, compared to 11% in the initial seeds (those recruited by advertisements). Using 10% as the base rate in the nonpeer recruitment group (no access to peer recruitment), we estimated sample size requirements by varying the proportion in the peer recruitment from 16% to 20%. With these assumptions, for our primary aim, we will need 219 smokers in each group to detect a difference of 10% (power=80%, α=.05). If we reduce the difference to 8% and 6%, we will need 319 and 525 participants in each group, respectively. Given that we will work with our panel to encourage recruitment of African American smokers in the peer recruitment group and may see bigger differences than those in our pilot study, we will have adequate power, particularly with the proposed sample size of 600 in each recruitment method. For recruitment time, previous trials estimated that the mean number of days to recruit a sample of 700 smokers was 244 (SD 81) days [27,40]. Assuming that peer recruitment proceeds with the same rate and SD, we can detect a difference in recruitment time as low as 14 days. Since we expect the comparison rate to be much slower, we are adequately powered to detect differences with a sample of 600 (power=80%).

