#### Hypothesis 2: Repeated Use of Website

We used the method published by Whitehead to calculate power for this hypothesis [41]. In our previous work, we found a linear association between the 6-month cessation and repeated use by using the repeated use scale. For every increase by one in this scale, odds of smoking cessation increased (OR 2.10, 95% CI 1.03-4.30) [39]. With the current sample size of 300 per group, we can detect a difference a cumulative odds ratio of 1.7. Thus, our study is adequately powered to measure a reasonable difference in the repeated use measure.

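### Hypothesis 2 toolset contrasts compare a mix of randomised direct recruits and non-randomised peer recruits with direct recruits only, so recruitment source confounds them

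*Protocol article*

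**What the plan says.** All references are to the Protocol article.

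- **Hypotheses (Introduction, Textbox 1).** Hypothesis 2 concerns repeated use in four groups formed by toolset access and CTHC type. H2A compares the fully enhanced group with (1) toolset only, (2) recommender only and (3) standard. H2B compares toolset with standard, and H2C recommender with standard.
- **Allocation (Study Design; Figure 1 caption).** Everyone is randomised to recommender or standard CTHC. Toolset allocation then depends on recruitment source. Direct recruits are randomised to toolset or no toolset, but "All peer recruited participants will receive access to the peer recruitment toolset".
- **Model (Statistical Analyses).** Hypothesis 2 is tested with a generalised linear model "which includes indicators of peer recruitment and recommender CTHC and the interaction between the two indicators as independent variables".
- **Source differences (Statistical Analyses).** The article lists "covariates (minority status, education, readiness to quit, and income) that have been shown to differ between the peer recruitment and standard recruitment".
- **Size.** The goal "is to recruit 1200 smokers to test our effectiveness and dissemination hypotheses". For Hypothesis 2: "With the current sample size of 300 per group, we can detect a difference a cumulative odds ratio of 1.7". For Hypothesis 1 the article refers to "the proposed sample size of 600 in each recruitment method".

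**The concern.** Every participant without the toolset is a direct recruit, whereas the toolset groups contain direct recruits randomised to it and peer recruits who received it by rule. A comparison across toolset levels therefore also compares two kinds of recruit. The article itself says the sources differ on readiness to quit, which plausibly bears on how often someone returns to a cessation website.

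Analysing by intent to treat does not help, because peer recruits were never randomised to the toolset. An apparent toolset effect on repeated use could reflect who was recruited, and a real one could be hidden. The interaction term is exposed too: it sets the CTHC effect in a mixed population against the CTHC effect in direct recruits, so it would pick up any difference in CTHC effect by source.

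The same allocation rule also determines the group sizes, and these do not match the ones used for power.

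**Working it through.** **1. Which contrasts are affected**

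| Contrast | Composition | Confounded by source? |
|---|---|---|
| H2A v (1), toolset only | mixed v mixed; CTHC randomised | No |
| H2A v (2), recommender only | mixed v direct only | Yes |
| H2A v (3), standard | mixed v direct only | Yes |
| H2B | mixed v direct only | Yes |
| H2C | direct only v direct only; CTHC randomised | No |

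Hypothesis 3 compares CTHC arms, randomised for everyone, so it is not confounded by source.

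**2. The plan's own figure**

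Whitehead's formula: V = n1·n2·N / [3(N+1)²] × (1 − Σp̄³), with power = Φ(ln OR × √V − 1.96). The article gives neither category proportions nor a power level for Hypothesis 2, so 1.7 cannot be reproduced uniquely. With assumed control distributions from 33/33/33 to 85/10/5, the odds ratio detectable at 80% power with 300 v 300 runs from 1.52 to 1.78 (1.69 at 80/15/5). The stated 1.7 is plausible for 300 v 300. Under 50/30/20, used below, the detectable value is 1.53.

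**3. Cell sizes implied by the allocation rule**

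Let D be direct and P peer recruits, D + P = 1200. Each no-toolset cell is D/4; each toolset cell is D/4 + P/2.

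| P | No-toolset cell | Toolset cell | Randomised share of toolset cell |
|---|---|---|---|
| 0 | 300 | 300 | 100% |
| 200 | 250 | 350 | 71% |
| 600 | 150 | 450 | 33% |
| about 720 | about 120 | about 480 | 25% |

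The last row uses the pilot yield reported under Access to a Peer Recruitment Toolset: 569/190 = 2.99 recruits per smoker with access. With half of direct recruits given access, D = 1200 / (1 + 2.99/2), about 480. The P = 600 row applies if 600 in each recruitment method refers to recruitment source. Four cells of 300 require P = 0.

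**4. Illustration of the bias**

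Assumptions, none from the document: control distribution 50/30/20, toolset with no effect, peer recruits' cumulative odds of repeated use equal to g times those of direct recruits. At the pilot yield, 75% of a toolset cell are peer recruits.

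For g = 0.75:
- Any use: direct odds 1.00; peer proportion 0.75/1.75 = 0.429. Mixture 0.25×0.5 + 0.75×0.429 = 0.446, odds 0.806, OR 0.806.
- Top category: direct odds 0.25; peer proportion 0.1875/1.1875 = 0.158. Mixture 0.25×0.2 + 0.75×0.158 = 0.168, odds 0.2025, OR 0.810.
- Geometric mean 0.81. At 480 v 120, V = 25.9, ln(OR)×√V = −1.08, and the two-sided 5% test rejects about 19% of the time.

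| g | Apparent OR, inert toolset | ln(OR)×√V | Rejection rate |
|---|---|---|---|
| 0.75 | 0.81 | −1.08 | 19% |
| 0.60 | 0.69 | −1.87 | 46% |
| 1.5 | 1.36 | 1.62 | 37% |

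**5. Detectable odds ratio, 80% power, 50/30/20**

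| Comparison | Detectable OR |
|---|---|
| 300 v 300, as planned | 1.53 |
| 480 v 120, unrestricted cells at pilot yield | 1.70 |
| 120 v 120, direct recruits only at pilot yield | 1.96 |

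**The case against.** Several points on the other side carry weight.

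- **Adjustment may already be intended.** Statistical Analyses promises to account for imbalances between groups, and an article may leave a covariate list to the analysis plan. This covers measured characteristics only, however, and cannot restore randomisation. The three-step strategy for source differences names smoking cessation as its outcome, not repeated use.
- **The estimand is arguable.** The Discussion says recruitment and use together evaluate the dissemination strategy, so source mix could be seen as part of that strategy. Hypothesis 2, though, is worded in terms of exposure to the toolset. If the model's peer-recruitment indicator instead means source, the model does not test Hypothesis 2 as worded. Either way the text needs settling.
- **The bias is not quantified by the document.** No figure gives repeated use by source. A reader might infer that the toolset result must be inflated, or must be masked; neither can be said.
- **Power.** A reader might infer that the unequal split by itself defeats the plan. It does not: at 480 v 120 the detectable odds ratio is 1.70 under the assumed distribution, matching the stated figure. Most of the loss comes from restricting to direct recruits.
- **Function count.** A reader might infer from "This is an ordinal scale of the number of Decide2Quit functions used after the first DISC visit" that opening the toolset itself scores as use. The article does not say the toolset is one of those functions.
- **Complier-average analysis.** This is planned for the recruitment comparison with cessation as outcome, so it is not part of this point.

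**Conclusion.** The point holds for three contrasts: H2B, and H2A against the recommender-only and standard groups. As written they are not randomised comparisons of the toolset. That follows from the allocation rule and the stated model, with no numerical assumption beyond some peer recruitment taking place. The interaction term is exposed through any difference in CTHC effect by source.

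The odds ratios and rejection rates are illustrations that depend on an assumed source effect, an assumed outcome distribution and the pilot yield. They show that moderate source differences could matter, not that they will.

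The group size of 300 is inconsistent with the allocation rule once anyone is peer recruited within a total of 1200. It is not impossible: with no peer recruits it holds, and the confounding then disappears as well.

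A reader might infer that the trial's effectiveness result is compromised. The documents do not support that. CTHC is randomised for everyone, so Hypothesis 3, H2C and H2A against toolset only are free of source confounding, although H2C has fewer participants because both its cells lack the toolset. Website engagement is a secondary outcome, so this should be fixed but does not threaten the primary analysis.

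**What to change.** 1. Base the Hypothesis 2 toolset and interaction contrasts on directly recruited participants. Alternatively, add a peer-recruited indicator and its interaction with CTHC; since no peer recruit lacks the toolset, the toolset effect is then again estimated from direct recruits.
2. Keep peer recruits in the CTHC contrasts, to which they were randomised.
3. Report the comparison of all participants by toolset access as secondary, described as non-randomised and adjusted for measured source differences.
4. State that the model's peer-recruitment indicator means toolset access.
5. Restate Hypothesis 2 power by expected direct recruits per cell, giving the assumed category proportions and power level.

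The cost is a change of wording; recruitment source is already needed for allocation, so no new data are required. The price is precision: the stated detectable odds ratio for the toolset contrasts rises, for example from 1.53 to about 1.96 at the pilot yield under the assumed distribution.

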**Baseline measures**			
	Demographics	Age, gender, race, ethnicity, education level Contact Information	Reach
	Smoking habits	Current smoking habits	Reach
	Quit attempts	Readiness to quit Nicotine dependence Nicotine replacement therapy use E-cigarette use	Reach
	Family-based intervention and social network	Household status Smokers in social network Interest in family-based intervention	Reach
	Reach and registration	Number of users who saw and clicked on online advertisements Number of users who registered following online advertisements	Reach, Adoption

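### Step 1 of the peer v standard recruitment comparison of cessation names four covariates and leaves out nicotine dependence, baseline smoking, smokers in the social network and household status, so residual confounding may remain

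*Protocol article*

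**What the plan says.** The last part of Statistical Analyses describes three steps for comparing smokers by recruitment route. Step 1 begins: "First, we will collect data on covariates (minority status, education, readiness to quit, and income) that have been shown to differ". The difference meant is the one by route seen in earlier work. The article then gives the use of these covariates: "We will use these variables to adjust our overall models with the outcome of smoking cessation". The contrast in those models is peer against standard route. Step 2 adds a marker for each recruiter as a fixed effect. Step 3 adds complier-average causal effect (CACE) models after the first two adjustments.

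The baseline part of Table 1 lists these items:
- demographics: "Age, gender, race, ethnicity, education level" (income is not listed)
- current smoking habits
- quit-attempt items: "Readiness to quit Nicotine dependence Nicotine replacement therapy use E-cigarette use"
- family and network items: "Household status Smokers in social network Interest in family-based intervention"

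Study Design says: "The peer recruitment allocation will depend on the recruitment source". Directly recruited smokers are randomised to have the toolset or not. All peer-recruited smokers get it.

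**The concern.** Nobody is randomised to arrive through a friend or through an advertisement. A comparison of quitting by recruitment source therefore relies on covariates to make the groups comparable, and step 1 is where the article names them. The stated reason for choosing them is that they differed by route in an earlier study. That is half of what makes a confounder. The other half is a link to the outcome, and this selection rule does not look for it.

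Nicotine dependence and baseline cigarette consumption are natural candidates as predictors of quitting. Smokers in the social network is a candidate because the recruitment mechanism itself ties it to the route. If these variables differ between routes and also predict quitting, a difference in quit rates could be read as an effect of the recruitment route when part of it is a difference in who was recruited. At stake is the interpretation of a secondary comparison that the Discussion itself calls an inherent challenge and says the analysis plan addresses.

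**Working it through.** **1. Step 1 list set against Table 1.** The article states no figure for this point, so there is none to reproduce.

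| Variable | In Table 1 baseline? | Named in step 1? |
|---|---|---|
| Minority status (race, ethnicity) | yes | yes |
| Education | yes | yes |
| Readiness to quit | yes | yes |
| Income | not listed | yes |
| Nicotine dependence | yes | no |
| Current smoking habits | yes | no |
| Smokers in social network | yes | no |
| Household status | yes | no |

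**2. Why the network item is tied to route.** Study Participants admits only current smokers. Under Access to a Peer Recruitment Toolset, participants recruit from their own social network. Every peer recruit therefore has at least one network member who was smoking when that person enrolled. Someone who arrives from a search advertisement or ResearchMatch need not.

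**3. Whether other text fills the gap.**
- The general rule in Statistical Analyses examines balance by study group and accounts for imbalances in multivariable analysis. Its parenthesis covers demographics and prebaseline smoking behaviours, so dependence and cigarettes smoked could enter. Entry depends on observed imbalance, the rule is written for study groups, and it does not name network or household items.
- The rule written for the two recruitment methods, under Hypothesis 1, adjusts the recruitment-time outcome and not cessation.
- The recruiter marker in step 2 addresses clustering and does not replace the recruit's own characteristics.

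**4. Illustration of size, on assumed inputs.** The 15% quit rate is the control rate under Sample Size, Hypothesis 3. The odds ratios and prevalences are assumptions that do not come from the documents. Take one omitted binary factor, independent of the adjusted covariates, and no true effect of route. Let a and b be the quit rates without and with the factor, and p0 and p1 its prevalence in standard and peer recruits.

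Solve (1 − p0)a + p0·b = 0.15, with odds(b) = OR × odds(a). Then the spurious difference = (p1 − p0)(b − a).

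- Mild: OR 0.7, p0 = 0.40, p1 = 0.50. a = 0.1676 and b = 0.1236. The difference is 0.10 × (−0.0440) = −0.0044, or −0.4 points.
- Strong: OR 0.5, p0 = 0.30, p1 = 0.60. a = 0.1736 and b = 0.0950. The difference is 0.30 × (−0.0786) = −0.0236, or −2.4 points.

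For scale, with the 600 per recruitment method given under Sample Size, Hypothesis 1, SE = √(0.15 × 0.85 × 2/600) = 0.0206, or 2.1 points. The bias is then 0.0044/0.0206 = 0.2 SE to 0.0236/0.0206 = 1.1 SE. The two-sided 5% error rate, Φ(−1.96 + e) + Φ(−1.96 − e) with e the bias in SE units, becomes about 5.5% to 21%. The negative sign follows only from assuming that the factor lowers quitting and is commoner in peer recruits.

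**The case against.** The strongest reply has four parts.

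- **The list may not be closed.** Step 1 says that these variables will be used, not that no others will, and a condensed article may leave the full covariate list to the analysis plan. This stands in part. It is why the conclusion is possible residual confounding and no more. But the article does name a set and the reason for choosing it, and that reason does not lead to predictors of quitting.
- **The general imbalance rule may cover smoking behaviours.** This also stands in part, as set out in the working. It does not reach the network and household items.
- **The stakes are limited.** No numbered hypothesis concerns cessation by recruitment source. Hypothesis 3 compares randomised recommender and standard CTHC and is untouched. This stands in full.
- **The contrast may not be recruitment source.** If peer recruitment here means randomised toolset access among directly recruited smokers, this confounding does not arise. The text does not clearly separate the two contrasts, so the ambiguity itself needs resolving.

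A reader might also infer more than the documents support:
- **That the comparison certainly stays confounded.** Nothing in the documents gives the size or direction of a bias.
- **That smokers in the household are recorded at baseline.** Table 1 lists household status only.
- **That the CACE models simply inherit the gap.** They follow steps 1 and 2, but they set compliers against would-be compliers and rest on their own assumptions and on the randomised part of the toolset allocation.

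**Conclusion.** The point holds in a limited form. For a comparison that is not randomised if it is by recruitment source, step 1 does not name four baseline items that Table 1 collects, and one of them, smokers in the social network, is linked to the peer route by design. The general imbalance rule is only a partial safeguard. Residual confounding may remain.

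The range of 0.4 to 2.4 percentage points shows only what one omitted factor could do under the assumed odds ratios and prevalences. At the low end it is negligible. It is not an estimate for this trial. The conclusion bears on the secondary comparison by route, not on the primary effectiveness result or on randomised toolset access among direct recruits. The absence of income from Table 1 is a separate, smaller mismatch.

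**What to change.** - In step 1, keep minority status, education, readiness to quit and income. Add nicotine dependence, baseline cigarettes smoked, number of smokers in the social network and household status, all fixed in advance and included whatever their observed imbalance. Use the network item as a number if it was recorded that way, since an any/none version should hardly vary among peer recruits.
- State whether the contrast is recruitment source or randomised toolset access. If both are intended, report them separately, and present only the second as randomised.
- Reconcile income with Table 1. If it was collected, list it there. If not, say that it cannot be adjusted for. Removing it without comment would discard a variable the article says differs by route, and adding it to the baseline form is too late, because the Abstract reports enrolment complete.

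The cost is a few sentences and a few model degrees of freedom. Table 1 already lists all four added items as baseline measures.
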